### Randomization and binding

This study will adopt wait list control with open labels, as binding is not possible. The sequence of subjects receiving interventions will be determined by randomization after the informed consent is being collected, of each slots of intervention will be separated by 6 months of waiting period. Statisticians independent from the project team will be given randomly generated treatment allocation within sealed, opaque envelops. During the initial health assessment, one of the envelops will be drawn and the participant will be allocated with the drawn sequence after they consent to participate in this trial. During the waiting period, the experimental group of subjects will be allocated to usual care with no intended treatment given.

### Control group selection

This study will have a wait-list control, where the control will receive usual care of health information on diabetes risk management, conventional weight-control management and dietary education during the 6 months waiting period. On completion of the waiting period, the nurse and dietitian will invite the control group's participants for a face-to-face consultation, where the clinical staff and lay health workers will have a chance to identify their service needs and give tailored care plans.

### Primary and secondary outcomes

This controlled trial will use a wide range of clinical and patient-reported outcomes measures to assess the cost-effectiveness of this intervention. The outcomes are set with reference to the *Medical Research Council framework for evaluating complex intervention* (31) and on the *American Diabetes Association's Standards of Medical Care in Diabetes 2021* for diabetes research (32).

We have two primary outcomes in this trial. Glycated hemoglobin (HbA1c) will be measured by self-test kit (Polymer Technology Systems Inc., Whitestown USA), and fasting blood sample for plasma glucose will be measured by blood glucose monitor (ForaCare Inc, Moorpark USA).

We also included anthropometric measures, self-reported outcomes, dietary consumption patterns, and patients' satisfaction of the lay health worker intervention as secondary outcomes. Body mass index will be calculated with body weight (kg) and body height (m) measured, and waist circumference of the participants will be measured to the nearest 0.1 cm. We will measure the percentage body fat using bioimpedance analysis with BC240 (Tanita Corp., Tokyo Japan). Participants' risk of depression, anxiety and stress will be measured by The Depression, Anxiety and Stress Scale - 21 Items (DASS-21) (33). Self-reported health related quality of life will be measured using EQ-5D-5L (34). Consumption pattern of the participants as recorded by three-day food records to capture the day-to-day variations of the participants' diet (35). In order to improve the validity of the food record collected, a written guideline will be given to the participants to guide their completion of the dietary records, together with a filled template and size of standard food containers for reference. Firstly, participants are instructed to complete the food record in 2 weekdays and 1 weekend day. Also, they are encouraged to consume a typical diet, record every meal they have consumed, using bowls and other utensils to measure the amount of foods and drinks, record the portion of pre-packaged foods stated on the food labels, record the ways of cooking, record the recipes and take a picture of the meals consumed. Upon the completion of the food record, a registered dietitian and a group of lay health workers trained by the dietitian will call the participants to review the accuracy and completeness of the food record. Visual aids are used including pictures of foods and food models. The complete food record is then input into Food Processor by an experienced research assistant to generate nutritional values of the participant's diet (36). Patients' satisfaction toward the lay health worker intervention will be measured with a 5-points Likert scale in a self-administered questionnaire to be filled by the patients at the exit assessment for the assessment, with a higher score indicating a more satisfied care experience in the intervention.

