**Methods and analysis:**

In this trial, 222 Chinese primary caregivers living in inadequate houses and with diabetes risk will be recruited *via* non-profit organizations serving in districts with low average household incomes and prevalent subdivided flats in Hong Kong. Adopting a 6 months wait-list control, participants will be randomized to receive a 6-months lay health worker intervention of 5 components, including (1) lay health worker training and support; (2) health professional training; (3) formulation of a targeted care plan for the health and nutritional needs of the families; (4) case management approach; and (5) financial subsidy for lay health workers to sustain the practice. The control group will receive usual care and health information on diabetes risk management. Glycated hemoglobin (HbA1c) and fasting blood glucose will be taken at the entry and exit assessment of this trial as primary outcomes.

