**Figure 1 F1:**
[figure not shown]
CONSORT workflow of this trial.

**Table 1 T1:** Minimal data set for trial registration.

**Data category**	**Information**
Primary registry and trial identifying number	Chinese clinical trial registry ChiCTR2100052080
Date of registration in primary registry	16-Oct-21
Secondary identifying numbers	N/A
Source (s) of monetary or material support	The Hong Kong jockey club charities trust
Primary sponsor	The Hong Kong jockey club charities trust
Secondary sponsor (s)	N/A
Contact for public queries	[name] DFPH Jockey club school of public health and primary care, The Chinese University of Hong Kong, China
Contact for scientific queries	[name] DFPH Jockey club school of public health and primary care, The Chinese University of Hong Kong, China
Public title	Lay health worker as an example of medical task-shifting: design of a pragmatic randomized controlled trial for diabetes prevention in people living in inadequate housing
Scientific title	Lay health worker intervention on diabetes management
Countries of recruitment	Hong Kong, China
Health condition (s) or problem (s) studied	Diabetes
Intervention (s)	Active comparator: lay health worker intervention
	Placebo comparator: usual care with diabetes control information
Key inclusion and exclusion criteria	Ages eligible for study: ≥ 18 years and < 65 years
	Sexes eligible for study: both
	Accepts healthy volunteers: no
	Inclusion criteria: adult patient (≥ 18 years and < 65 years) who is the major caregiver of households living in sub-divided flat units in Hong Kong
	Exclusion criteria: mentally incapable to give consent
Study type	Interventional
	Allocation: randomized intervention model
	Parallel assignment
	Wait-list control of 6 months waiting period
	Primary purpose: prevention
	Phase I
Date of first enrolment	Nov-21
Target sample size	222
Recruitment status	Recruiting
Primary outcome (s)	Glycated hemoglobin (HbA1c)
Key secondary outcomes	Body mass index; Waist circumference; Percentage body fat; 3-day food records; Depression, anxiety and stress as measured by DASS-21; Quality of life as measured by ED-5D-5L

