In order to compare the effectiveness of intervention between control and the intervention group at the exit assessment of intervention (6^th^ month), we will use repeated-measures Analysis of Variance (ANOVA) for parametric outcomes. We will consider the measures of data at baseline (0^th^ month) and covariates that are imbalanced in control and intervention groups when conducting ANOVA, and the effect size will be estimated by calculating the Cohen's *d* value. For non-parametric variables, the Friedman test will be done, and Kendall's W value will be produced for effect size estimation. For ordinal data, we will use Generalized Estimating Equations to compare groups at each follow-up (0^th^ month, 6^th^ month, and 12^th^ month), allocation group (intervention and wait-list control), time by group interaction, covariates that are imbalance between groups, and important socio-economic variables including sex, age, and education level. We will use an identify link function given a normal distribution of the captioned outcome. Also, Kaplan-Meier curves will be drawn to capture the comparison of diabetes-free survival in the intervention and control group. The level of significance is set at 5% m and *post-hoc* adjustment will be applied for multiple comparisons. Multiple imputations will be used whenever appropriate for missing data. In this analysis, all statistical analyses will be conducted using R and RStudio, and the Cohen's *d* value will be estimated using G^*^Power.

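### Table 1 names one primary outcome, the abstract and outcomes section name two, and the trial is sized on one, so the confirmatory test is not fixed

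*Protocol article*

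**What the plan says.** All references are to the protocol article.

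- **Abstract, Methods and analysis:** "Glycated hemoglobin (HbA1c) and fasting blood glucose will be taken at the entry and exit assessment of this trial as primary outcomes".
- **Primary and secondary outcomes:** "We have two primary outcomes in this trial". The first is HbA1c from a self-test kit. For the second, a "fasting blood sample for plasma glucose will be measured by blood glucose monitor".
- **Table 1, primary outcome row:** "Primary outcome (s) Glycated hemoglobin (HbA1c", and nothing further in that cell.
- **Table 1, key secondary outcomes row:** "Body mass index; Waist circumference; Percentage body fat; 3-day food records; Depression, anxiety and stress as measured by DASS-21", followed by quality of life. Fasting glucose is in neither row.
- **Sample size calculation:** 111 per arm (222 in total), from an HbA1c difference of 0.5%, an SD of 1.5, 80% power and 20% dropout. No difference or SD is given for glucose, and alpha is not divided.
- **Data analysis:** primary and secondary outcomes are compared between groups in the same general way. The significance level is 5%, and a post-hoc "adjustment will be applied for multiple comparisons". Neither the method nor the set of tests it covers is named.

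**The concern.** The abstract and outcomes section point to two primaries. Table 1 and the sample size point to one. These statements cannot all hold, and nothing in the article says which governs. It also does not say whether success needs either outcome, both, or one before the other.

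This matters because the success rule sets both the false-positive rate and the power. In an open-label trial, leaving it open also lets the emphasis follow whichever glycaemic measure turns out better, and a later report could be challenged against the single outcome in Table 1.

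**Working it through.** **Inputs.** From Sample size calculation: difference 0.5, SD 1.5, power 80%, dropout 20%, 111 per arm. From Data analysis: alpha 0.05. Sidedness is not stated; two-sided is taken here unless noted. The correlation between the two test statistics is not given, so 0, 0.5 and 0.8 are assumed.

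**The plan's own figure.** n per arm = 2 × [SD × (z for alpha + z for power) / difference]².

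- Two-sided: 2 × [1.5 × (1.960 + 0.842) / 0.5]² = 141.3, so 142 per arm. With dropout, 142 / 0.8 = 178 per arm (356 in total).
- One-sided: 111.3 per arm, close to the stated 111, but before any dropout allowance.

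So 222 does not reproduce at two-sided 5% with dropout. That is a separate matter. To isolate the effect of the unclear primary, the readings below start from the stated 80% power.

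**Reading 1: HbA1c alone is primary (Table 1).** One test at 5%, with no multiplicity cost.

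**Reading 2: either outcome suffices, each tested at 5%, no adjustment.** Family-wise error = P(max of |Z1|, |Z2| > 1.960) under a bivariate normal null.

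- Correlation 0: 1 − 0.95² = 9.75%
- Correlation 0.5: 9.1%
- Correlation 0.8: 7.8%

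**Reading 3: either outcome suffices, with Bonferroni at 2.5% each.** A two-sided 5% test with 80% power has an expected Z of 1.960 + 0.842 = 2.802. At 2.5% the critical value is 2.241, so power = Φ(2.802 − 2.241) = Φ(0.56), about 71%. If the stated 80% was one-sided, the same step at 111 per arm takes it from 80% to 70%. Restoring 80% two-sided at 2.5% needs 172 evaluable per arm instead of 142.

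**Reading 4: both must succeed, each at 5%.** Alpha is not inflated. If each test has 80% power, joint power = P(Z1 and Z2 both significant):

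- Correlation 0: 0.8² = 64%
- Correlation 0.5: 69%
- Correlation 0.8: 73%

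Joint power of 80% with independent, equally powered tests needs power √0.8 = 89.4% on each, or 186 evaluable per arm on the HbA1c inputs.

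**Reading 5: HbA1c first, then fasting glucose only if HbA1c is significant.** HbA1c keeps the full 5%, and family-wise error for the pair stays at 5%.

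**The case against.** The strongest reply is that Data analysis already promises a multiplicity adjustment, and that its method and scope are normally left to an analysis plan, which may exist unseen. That stands in part. The unnamed method is not a fault in itself, and the 7.8% to 9.8% range is not the error rate of the plan as written. It applies only if the adjustment does not cover the two primaries. An unseen analysis plan cannot, however, make Table 1 and the outcomes section agree on how many primaries there are.

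Stronger readings that a reader might infer, and why the document does not support them:

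- *Either the error rate exceeds 5% or HbA1c must be tested at 2.5%.* This leaves out the both-must-succeed and hierarchical readings, under which neither happens.
- *Multiplicity brings HbA1c power down to about 49%.* That is the Bonferroni figure at 89 evaluable per arm, but unadjusted two-sided power there is already only 60%. The gap from 80% to 60% comes from the sample size not reproducing.
- *The article contradicts the registry.* The registry record is not at hand; what can be shown is a conflict with Table 1. The absence of fasting glucose from the key secondary list is weak evidence on its own, because patient satisfaction, a secondary outcome in the text, is missing there too. The primary outcome row carries the conflict.

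It is also fair that keeping two primaries and correcting Table 1 would remove the contradiction.

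**Conclusion.** The point holds as an internal contradiction with an unfixed success rule. Table 1 has one primary, the abstract and outcomes section have two, the sizing covers HbA1c only at an undivided 5%, and no rule links the two outcomes.

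Its size is conditional. There is no cost if HbA1c is the sole primary or is tested first in a fixed order. Otherwise the consequence is an excess of 2.8 to 4.8 percentage points over a 5% error rate, a loss of about 9 points of HbA1c power, or joint power 7 to 16 points below 80%, depending on the rule. These figures rest on normal approximations, the assumed correlations and, for power, the stated 80% taken at face value. The joint-power figures also assume 80% power for fasting glucose, for which the article gives no inputs. This should be corrected before the analysis; it does not by itself invalidate the design.

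**What to change.** Make HbA1c at month 6 the single primary outcome, tested two-sided at 5%. This matches Table 1 and the outcome used for sizing. Make fasting glucose the first key secondary, tested only if HbA1c is significant, which holds family-wise error for the pair at 5%. Align the abstract, Table 1, the outcomes section and the registry entry.

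The work is text and registry alignment, with no new data or participants needed for this point. The downside is that fasting glucose loses primary status and cannot support a confirmatory claim if HbA1c fails.

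If the sponsor prefers two primaries, it should correct Table 1, state whether either or both must succeed and how alpha is allocated, give a difference and SD for fasting glucose, and restate the power to match.

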Training will be conducted in the way of interactive training workshops given by a nurse, a dietitian, and public health practitioners to provide the introduction of medication management, nutritional knowledge, and health promotion skills. In the training session, the lay health workers will be given a set of training manuals and resources to guide their involvement in the programme. The training manual will be developed with reference to the evidence from the literature review for other volunteer-based training programmes, such as the Get Healthy Information and Coaching Service provided by the New South Wales Government of Australia (26). The training manual will include roles and responsibilities clarification, training in communication skills, needs assessment skills, trust-building advice, health and safety in a home setting, coping strategies for handling unexpected events, and skills to conduct motivational interviewing. Additional resources such as the instruments to be adopted in needs assessment and continuous monitoring of the health of the families, the detailed workflow of carrying the assessments, knowledge on providing basic consultation and identifying life-threatening symptoms, and skills for infection control during the pandemic will be provided. Furthermore, stimulations on the health need assessment, reinforcing behavioral change, and health monitoring will be done in the workshops. This training workshop will be a co-creation of the dietitian, nurse, social worker and public health practitioner in our inter-disciplinary team, which will create and synergies and knowledge transfer of professional knowledge across dietetics, nursing, public health science and social care.

To ensure the quality of training, all the workshops are conducted in an interactive manner and all the lay health workers must achieve a passing grade in the phone practicum and participate in the debriefing. Each workshop has multiple discussion sessions and quizzes to answer questions and provide opportunities for practice. The quiz is in the form of multiple-choice questions, and instructor will discuss the answers with the lay health worker immediately. The main purpose of the quizzes is to ensure the lay health workers understand the main concept of training, and facilitate in-class discussion with the instructors. All answers could be found in the training materials provided.

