### Lay health worker intervention content

A tailored behavioral change plan will be co-formulated by the lay health workers and the healthcare professional to cater the health needs of the participants. Upon the collection of consent, a needs assessment will be conducted to understand the health and nutritional needs of the participants in the community settings. Then, the primary care workers (who is a nurse or dietitian in this trial) will provide a face-to-face initial consultation session with the trial participants, and identify tailored health goals corresponding to the needs of the participants. Toward the end of the initial consultation, nurse/dietitian will introduce lay health workers to the participants, provide necessary information to ensure smooth handover and handling, and facilitate the rapport building between lay health workers and the participants. Then, the lay health workers will formulate a tailored behavioral change plan according to the health goals set, discuss the feasibility and readiness of the plan with participants, and be responsible for the monitoring of the behavioral change, and managing the self-reported health status of the participants since then through telephone consultation, once 2–4-week for 6 months.

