This interventional will adopt a case-management approach. Upon the commencement of the tailored behavioral change plan, lay health workers will perform behavioral change monitoring through the 6-months period, under the supervision of the nurse/dietitian. The lay health workers will adopt a case-management approach, which each participant will be follow-up by the same lay health workers throughout the intervention, to allow the change monitoring to be done based on a trusted relationship. Each of the lay health workers will not be managing more than four families in the same period. To better facilitate behavioral change, the lay health workers will adopt the Stages-of-Change Model, which was developed by James Prochaska and Carlo DiClemente in 1983 (27). The model describes personal behavioral change in five stages, namely pre-contemplation, contemplation, preparation, action, maintenance, and relapse. Stage-of-Change Model is widely adopted in health psychology field and behavioral interventions (28, 29). In our proposed intervention, lay health workers will assess which stage the client is in, and motivate the client to move on to the next stage until the maintenance stage (27). During each follow-up, the lay health workers will review pre-established health goals with the participants, identify the facilitators and barriers of the participants' behavioral changes, and provide recommendations for the participants to overcome the identified barriers through motivational interviewing. Motivational interviewing is a “collaborative, goal-oriented style of communication with particular attention to the language of change,” with the aim to strengthen the person's motivation and commitment for the health behavior goal in an accepting and compassionate atmosphere (30).

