Alongside the case management duties, lay health workers will continuously assess the physical, mental, and nutritional health status of the participants through patient-reported outcomes. Lay health workers will maintain a close working relationship with the nurse and dietitian. Following each of the telephone follow-up, the lay health workers will participate in a group-based case de-briefing session where they can discuss the difficulties they encountered during the follow-up, and learn from each other's for better consultation skills. Lay health worker will review case progress with nurse/dietitian once every 2–4 weeks, and will discuss the motivators and barriers for the participants' behavioral changes to guide necessary amendments in the care plan. The participants are, therefore, under the co-management of the clinical professional (nurse or dietitian) and the lay health workers. For there is any undesirable outcome identified during the follow-up, the lay health workers will refer the participants for immediate intervention by the nurse and dietitians' management.

Lastly, financial subsidy will be provided to lay health workers to ensure the sustainability of their practice, and as a reward to honor their time spent on providing services to the participants.

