We will use a mixed-method approach to conduct the process evaluation on the participants. Quantifiable, routine data will be collected to evaluate the output of this intervention in corresponding to the five components of this intervention as described in Table 2, following with a *t*-test to compare intra-groups estimates to allow meaningful interpretations at the 6^th^ and 10^th^ month. The results from quantitative study part will provide a description for the overall execution of the intervention, which inform the answer for the following research questions: (1) what outputs were delivered to achieve the five components of the interventions; and (2) to which extend did the different stakeholders (study participants, healthcare worker, and lay health workers) complete/ adhere to the intervention? In complimentary to the quantitate research, the qualitative part of the mix-method study will be conducted in parallel. Two rounds of qualitative semi-structured, auto-taped individual interviews will be conducted at 6^th^ months (the completion of wait list control period) and 12^th^ month (project endpoint), to collect feedbacks from different stakeholders involved in this project. Project staffs (*n* = 2), lay health workers (*n* = 10), healthcare professionals participated (*n* = 5), NPO collaborators (*n* = 5) and study participants (*n* = 10) will be invited to participate in this study. Each individual interview will last for 1–1.5 h, with the following research questions to be answered: (1) what are the feedback and major concerns of the participants of the programme; (2) how to address these concerns in the second cycle of intervention?; (3) what are the facilitators and barriers in the programme delivery; and (4) how to enhance the facilitators or mitigate the barriers?, as guided by the *Consolidated Framework for Implementation Research* (37). Detailed interview questions can be found in Supplementary material S5. All the interviews will be conducted by research staff that is not involved in the delivery of this trial to ensure impartiality.

**Table 2 T2:** Outline of the process evaluation: output indicators.

**Component**	**Output**	**Indicators**	**Source of data**
1. Lay health worker training	More trained workers	Number of training sessions conducted	Administrative data
		Number of total lay health workers trained	Administrative data

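### Food records, a key secondary outcome, are reviewed by the roles that deliver the intervention, so at month 6 own-coach review is possible in one arm only

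*Protocol article*

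**What the plan says.** All references are to the Protocol article.

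**The outcome.** *Primary and secondary outcomes* states: "We also included anthropometric measures, self-reported outcomes, dietary consumption patterns, and patients' satisfaction of the lay health worker intervention as secondary outcomes". Diet is captured by a three-day food record, which Table 1 lists among the key secondary outcomes.

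**Who reviews it.** Once a record has been filled in, "a registered dietitian and a group of lay health workers trained by the dietitian will call the participants to review the accuracy and completeness" of it. A research assistant enters the record into the nutrient software after that call.

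**Who delivers the intervention.** According to *Lay health worker intervention content*, a nurse or dietitian sets the health goals at a first consultation. After that, "the lay health workers will formulate a tailored behavioral change plan according to the health goals set". Follow-up is by telephone every 2 to 4 weeks for 6 months, and "each participant will be follow-up by the same lay health workers throughout the intervention". During delivery, "lay health workers will continuously assess the physical, mental, and nutritional health status of the participants through patient-reported outcomes".

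**Masking and timing.** *Randomization and binding* states: "This study will adopt wait list control with open labels, as binding is not possible". Under *Control group selection*, controls are invited to meet clinical staff and lay health workers for care planning once the 6-month wait has ended.

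**A separation rule elsewhere.** For the qualitative interviews, *Data analysis* says: "All the interviews will be conducted by research staff that is not involved in the delivery of this trial to ensure impartiality". No similar sentence covers the food record.

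**The concern.** A food record is self-reported, and the review call is the last human step before it becomes data. A caller who asks about a missing snack or an unclear portion can influence what ends up in the record. If the caller is the person who has coached that participant's diet for six months, two things can happen. The participant may want to please the coach, and the coach may prompt with the agreed goals in mind.

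Error of this kind matters most when it differs between arms. At the month-6 comparison, only intervention participants have a coach, so only they can be called by one. A difference in reported diet could then partly reflect who made the call. Diet is also a direct target of the intervention: participants are chosen partly because they prepare the household's food, and the care plan covers nutrition. The dietary result is therefore likely to be read as evidence on mechanism.

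**Working it through.** The point rests on text, so most of the check sets statements side by side. The only arithmetic concerns the roster.

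**1. Is the call part of outcome measurement?** Yes. The order given is record, then review call, then data entry. The call comes before the nutrient values exist.

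**2. Are the callers delivery staff by role?** Yes. The article defines one group of lay health workers, those recruited and trained to deliver the intervention. The words about training by the dietitian do not clearly mark out a second group, because the delivering workers' own training also involves a dietitian: "Training will be conducted in the way of interactive training workshops given by a nurse, a dietitian, and public health practitioners". The dietitian is likewise a delivery role, since a nurse or dietitian sets the goals and co-manages the participant.

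**3. When, and in which arm, could a participant's own coach call?**

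| Assessment | Intervention arm | Wait-list arm |
|---|---|---|
| Baseline | No coaching yet | No coaching yet |
| Month 6 | Possible: the same worker throughout | Not possible: care planning starts after the wait |
| Month 12 | Possible | Possible |

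Month 6 is the exit assessment at which the arms are compared, and it is where the asymmetry lies.

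**4. Can the size be worked out?** Let p be the share of intervention-arm month-6 records reviewed by the participant's own coach, and δ the mean shift that such a review causes in a reported nutrient. The distortion of the arm difference from this route is p × δ. The documents give neither value.

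- If calls were always paired with the coach, p = 1.
- If calls were spread at random over 56 workers (step 5), p = 1/56 = 0.018, about 2%.
- If own-case calls were barred, p = 0.

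The plan is compatible with all three, and δ is unknown. A shift towards the coached diet is plausible, which would favour the intervention, but nothing in the documents proves its sign.

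**5. Is a separate caller feasible?** The inputs, from *Sample size calculation*, are 222 participants, four per worker, 20% worker dropout and 70 workers trained.

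- Reproducing the plan's figure: 222 / 4 = 55.5, rounded up to 56; 56 / (1 − 0.20) = 70. This matches the stated 70.
- Workers left after the planned dropout: 70 × 0.8 = 56.
- Possible callers other than the participant's own worker: 56 − 1 = 55.

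The planned pool is large enough to route each call to someone else.

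**The case against.** The strongest reply is that the point rests partly on silence. The article never says that a participant's own worker makes the call. The callers might be a subset briefed for this task, and rosters and scripts often sit in a full protocol or manual that is not shown here. This stands as a limit on the claim: own-coach review is left open, not stated. It does not remove the point, because the article does more than omit detail. It places delivery staff inside the measurement of an outcome.

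Second, there are safeguards. Records are written before the call, with meal photographs, food-label portions, recipes, a completed template and container sizes for reference. These narrow the room for prompting but do not close it, since the call exists to check and complete the record.

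Third, controls also receive dietary education, and all participants know their arm, so social desirability exists in both arms whoever calls. That is correct. Only the part tied to one's own coach is confined to one arm at month 6.

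Fourth, the impartiality rule for the qualitative interviews covers a different procedure, so its absence here is no contradiction. That is also correct. The rule shows only that separating staff from delivery is something this team already does.

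A reader might go further and infer that coaches do review their own cases, that the dietary result is therefore biased, or that callers rewrite the records. The text supports none of these: it says review, gives no pairing of callers with cases, and offers no basis for a size. Nor does it support extending the point to waist circumference or the exit satisfaction questionnaire. The article does not say who measures the waist, and the questionnaire is self-administered.

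**Conclusion.** The point holds in limited form. The plan assigns review of a key secondary outcome to the roles that deliver the intervention, in an open-label trial, with no stated bar on reviewing one's own cases. At month 6 this exposure can arise in the intervention arm only, and it could bias the dietary comparison, plausibly in favour of the intervention.

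The size cannot be computed. HbA1c and fasting glucose do not depend on the food record and are not affected. The conclusion assumes that the food-record callers come from the same pool as the delivering workers, which is the natural reading because no other pool is described, and that no separation rule exists in a fuller document. This is a cheap improvement, not a defect that threatens the primary result.

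**What to change.** In *Primary and secondary outcomes*, add a statement to this effect:

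- At every assessment and in both arms, the food-record call is made by a trained worker or dietitian who is neither that participant's lay health worker nor the treating nurse or dietitian.
- The caller follows a fixed script and works from a record that does not show the arm.
- The research assistant enters the data under an ID that does not reveal the arm.

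Naming the treating nurse or dietitian matters: a rule limited to the lay health worker would still let the clinician who set the goals review the record.

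The cost is protocol wording and a call roster, with no added staff or visits. Scheduling takes a little more work. Masking will be imperfect, because some participants may reveal their arm during the call and the group debriefings may make cases known to other workers. Even so, separating the caller from the coach removes the route that can operate in one arm only.
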